## Abstract

**Background:**

Attention deficit/hyperactivity disorder (ADHD) is the most prevalent neurodevelopmental disorder worldwide, affecting approximately 5%‐7% of school-aged children and 2%‐5% of adults worldwide. However, there is still no reliable diagnostic tool for it. The lack of specific biomarkers further complicates the accurate diagnosis of ADHD.

**Objective:**

The SINCRONIA study seeks to develop and optimize an electroencephalogram (EEG)-based ADHD diagnostic classification algorithm by identifying biomarkers that provide optimal diagnostic performance.

**Methods:**

This protocol introduces a single-center, case-control study involving at least 165 participants, aged between 7 and 12 years, that is being conducted at the Puerta de Hierro University Hospital in Madrid, Spain. Participants will be allocated to 3 groups, including ADHD predominantly inattentive, ADHD predominantly combined or hyperactive/impulsive, and a control group, according to the best estimated diagnosis based on clinical interviews and a neuropsychological assessment that includes the Conners Continuous Performance Test. In addition, an EEG recording will be conducted separately, and functional connectivity metrics will be used to characterize brain networks associated with inhibitory control. The index test is expected to match or improve the clinical diagnosis of ADHD in children aged between 7 and 12 years and provide a set of eventual biomarkers that maximize diagnostic performance and provide pathophysiological clues.

**Results:**

The SINCRONIA study began screening and recruitment in March 2023. Recruitment ended on December 11, 2024. A total of 165 eligible participants were enrolled.

**Conclusions:**

The SINCRONIA project is a high-quality, large-scale, unicenter study devoted to improving the objective diagnosis of ADHD by using EEG biomarkers. The EEG-based ADHD diagnosis is expected to have greater sensitivity and specificity than the Conners Continuous Performance Test.

## Introduction

Attention-deficit/hyperactivity disorder (ADHD) is a neurodevelopmental disorder characterized by inappropriate levels of inattention, hyperactivity, or impulsivity, typically emerging in childhood with a relatively high prevalence [1]. Reliable estimates place the prevalence above 5% in children and adolescents and 2.5% in adults [2-5]. However, these rates vary by country, with the prevalence reaching 11.4% in American children aged 3-17 years in 2022, according to the Centers for Disease Control and Prevention [6].

ADHD is linked to neurocognitive deficits and impairments in psychosocial and vocational functioning, including increased mortality and suicide rates [7-12]. Neurocognitive deficits span a broad range of functions, including working memory, inhibitory control, and vigilance [13], as well as imbalances between immediate and delayed rewards [14], processing speed [15], and motor activation and control [16]. Furthermore, ADHD often co-occurs with other psychiatric disorders such as generalized anxiety, major depression, bipolar disorder, substance use, and conduct disorders; or with other neurodevelopmental disorders [17,18].

Accurate diagnosis is crucial for effective treatment planning and improving clinical research. Efforts to refine psychiatric nosology by exploring connections between neurobiology and psychopathology are underway [19-21] with a key advancement being the identification of biomarkers for psychiatric disorders [22,23]. Advances in understanding the pathophysiology of ADHD have highlighted alterations in noradrenergic signaling within posterior attentional circuits [24], disruptions in dopaminergic pathways across various systems [25], dysfunction of the default mode network [26], and delayed development of the frontal cortex. Despite these insights, little progress has been made in classification and diagnosis, as reflected by the fact that neither the *DSM-5* (*Diagnostic and Statistical Manual of Mental Disorders* [Fifth Edition]) nor the *ICD-11* (*International Classification of Diseases, 11th Revision)* grants a significant role to neurobiology.

Unfortunately, ADHD diagnosis remains inaccurate, partly due to its multifactorial etiology, psychiatric comorbidities, and neurocognitive and brain alterations. Although diagnosis is based on a comprehensive evaluation of current and past symptoms and functional performance, overlapping symptoms with other disorders—such as mood or learning disorders—and frequent co-occurrence with conditions like autism spectrum disorder (ASD), learning disabilities, personality disorders, or substance use further complicate differential diagnosis [27-31]. While some authors contend that ADHD has been overdiagnosed [32-35], others dispute this view [29,36]. Additionally, assessing the widespread impact of ADHD on various life areas with limited consultation time presents a challenge, requiring evaluation of multiple contexts [30].

ADHD is a dynamic condition where slowly developing neurobiological deficits are rapidly influenced by maturation and compensatory mechanisms, resulting in significant heterogeneity both across individuals and within the same individual over time, thereby complicating both diagnosis and treatment [37]. This heterogeneity has driven increased neuroimaging research and the search for biomarkers [38]. Functional magnetic resonance imaging (fMRI) studies have revealed delayed cortical development—especially in the frontal, temporal, and parietal regions—and disruptions in connectivity and default mode network functionality [39,40]. Moreover, deficits in working memory and inhibitory control have been linked to underactivation in frontoparietal and ventral attention circuits, which play key roles in executive function and attention reorientation [41]. Additionally, reduced activation in the ventral striatum has been associated with altered reward processing [42]. Research also indicates a loss of the typical counter-regulation between cognitive control and default mode networks during rest [36], with some studies suggesting compensatory hyperactivation in motor and visual areas [43]. Importantly, much of the observed heterogeneity may stem from the fact that ADHD subtypes or syndrome-level distinctions are often collapsed into single-group analyses, obscuring meaningful neurophysiological differences. Studies that stratify participants by ADHD subtype have begun to reveal distinct neural signatures and developmental trajectories, which may prove crucial for biomarker discovery and personalized intervention design [44].

These findings underscore the complexity of diagnosing and understanding attention disorders, highlighting the need for more precise and scalable diagnostic tools. In this context, electroencephalogram (EEG)-based techniques have gained increasing interest due to their ability to track dynamic interactions across large-scale brain networks with millisecond temporal resolution [45,46]. Unlike fMRI, EEG can directly measure neural activity and is better suited to capture transient cognitive processes, such as inhibition and attentional shifts, key domains affected in ADHD. Source-level EEG analyses further enhance spatial resolution, making it a practical and cost-effective alternative to higher-end techniques like magnetoencephalography in clinical research [47]. When applied to stratified samples reflecting distinct ADHD subtypes, EEG may help reveal subtype-specific connectivity patterns that are obscured in traditional binary comparisons. This supports its growing potential not only as a complementary biomarker platform but also as a tool for advancing precision diagnostics in neurodevelopmental disorders.

The SINCRONIA study builds on the 2 attention-control networks model developed by Corbetta et al [48]. The dorsal attention network (DAN) exerts top-down control by maintaining focus on task-relevant information while filtering out distractions, thus ensuring sustained attention. In contrast, the ventral attention network (VAN) evaluates each incoming stimulus based on its novelty and importance. When a stimulus is deemed high priority, the VAN activates—interrupting the DAN’s filtering process—and sends signals to trigger executive control, reorienting attention and prompting the appropriate response [49-51]. Conversely, if the stimulus is considered of low priority, the VAN deactivates, and the DAN’s inhibitory influence is reinforced, preventing unnecessary shifts in attention [48,52,53].

While structural brain alterations in ADHD are acknowledged [54], functional changes—reflecting the interactions within neural circuits—hold greater diagnostic relevance [30]. Although EEG’s diagnostic utility at the time of this writing is limited, its high temporal resolution, accessibility, and low cost support its potential in developing tools and identifying biomarkers [55,56]. Capturing transient neural dynamics has shown promise [57], and using multivariate methods with machine learning (ML) significantly enhances accuracy, especially when incorporating signal synchronization metrics [55]. However, existing EEG studies for ADHD detection remain suboptimal as diagnostic tools [58,59]. For all these reasons, the SINCRONIA study aims to develop an ML-based classification algorithm using EEG brain connectivity metrics and to determine the biomarkers that maximize the diagnostic performance on the Bit task (hereafter referred to as the index test).

The primary objectives of our study are:

To demonstrate that the diagnostic performance of the index test (EEG-based)—determined against the final diagnostic judgment of the study’s principal investigator (PI) following a comprehensive clinical assessment—exceeds a predefined minimum threshold of clinical acceptability.To identify the biomarkers that optimize the diagnostic accuracy of the index test.

Secondary objectives are the following:

To develop and optimize a diagnostic classification algorithm based on selected biomarkers—identified in accordance with the primary objectives—to differentiate between controls, ADHD predominantly inattentive (without hyperactivity), and ADHD combined or hyperactive/impulsive (with hyperactivity) through classification models.Investigation of factors influencing diagnostic performance, including patient demographics and clinical characteristics of ADHD, as well as health care provider factors (eg, specialty and experience).To evaluate and compare the diagnostic performance of the index test—determined against the final diagnostic judgment of the study’s PI following a comprehensive clinical assessment—with that of the Continuous Performance Test Third Edition (CPT-3).Assessment of the clinical utility and value of the index test.

Tertiary objectives are the following:

To investigate the construct validity of sluggish cognitive tempo (SCT) in comparison to ADHD diagnosis.To optimize the preprocessing automatic system for artifact removal in EEG signals.To explore Bayesian mathematical models and their application to brain functional connectivity patterns.

## Methods

### Study Design

This is a noninterventional, case-control, cross-sectional, and assessor-blinded study, which is part of the development of a medical diagnostic test. This manuscript describes the latest version of the study protocol (HUPH-BP-BMCCEEG-CC22 version 4.0, approved on June 7, 2024, as Amendment 4), which was reviewed and approved by the appropriate ethics committee (see below). In order to allow for more complete and detailed reporting, we adhere to 2 acceptable reporting guidelines that match the study design: the Standards for Reporting Diagnostic Accuracy Studies (STARD; Checklist 2) and the SPIRIT (Standard Protocol Items: Recommendations for Interventional Trials) 2025 checklist (Checklist 1) of items to address in a randomized trial protocol, though, *sensu stricto*, our study is not a randomized trial. Following the terminology of the STARD, the EEG and the algorithms used to analyze the EEG data will be regarded as the index test, and the executive control task during which brain connectivity metrics will be pursued will be regarded as the index task. The best estimated diagnosis based on clinical interviews and neuropsychological assessment will be regarded as the reference test. To minimize bias, the PI establishing the reference standard will not perform EEG analyses or access EEG results. Blinding to index test results will be maintained, as no diagnostic or therapeutic decisions will be based on these findings. Consequently, no clinical decision will be influenced by information from the index test. Likewise, the team in charge of EEG processing will not have access to the clinical diagnosis data during data collection for the study. Participants will be categorized into 3 groups, including ADHD predominantly inattentive, ADHD combined or hyperactive/impulsive, and a control group, based on clinical evaluation including the reference CPT-3.

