### Planned Data Analysis

This clinical study focuses on the characterization and initial validation of an experimental medical diagnostic test under development. To avoid bias, the physicians involved in diagnosing and selecting the study groups will not participate in the analysis. Furthermore, missing data will not be imputed. In addition, indeterminate index test or reference standard results will not be allowed, as a positive or negative diagnosis will be required according to the previously defined cutoffs. Analyses will be performed on complete cases within each analysis set. The planned sample size (Multimedia Appendix 1) includes a margin for nonevaluable data (10% added for nonassessable data-complete-case analysis). No interim analyses or stopping rules are planned.

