#### Diagnostic Performance of the Index Test

The primary parameters are the classification probabilities of the index test relative to the reference test. In addition to these classification probabilities, positive and negative predictive values (PPV and NPV, respectively) and diagnostic likelihood ratios will be calculated. Inferences will be made by calculating 95% asymmetric rectangular confidence regions for each pair of interest values (TPF and FPF), (PPV and NPV), and (DLR^+^ and DLR^−^). Confidence regions will be calculated from the cross-product of the 97.5% confidence intervals of each component in each pair. Sensitivity values will be assessed for noninferiority (and potentially superiority), while specificity will be evaluated for strict superiority. In addition to naive predictive value estimates, which will be biased by design, other estimates will be adjusted using external prevalence data and diagnostic likelihood ratios or Bayesian multiplication factors to mediate prior and posterior probabilities:

, (2)$$logit\;PPV=logit\;\rho +\log{DLR}^{+}$$

, (3)$$logit\;NPV=-logit\;\rho \;+\;-\log{DLR}^{-}$$

where ρ is the prevalence in the target population (7.0% [71]). Clinical information and reference standard results will not be available to the performers of the index test. Furthermore, the reference standard will be performed after the index test. Moreover, performers of the index test will neither be involved in the technological processing nor the statistical analyses of either the index or the reference standard tests. Finally, cross-tabulation of the index test results (or their distribution) by the results of the reference standard will be considered.

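### The EEG-processing team is masked to diagnosis only during data collection, and no lock on cleaning settings or assessable recordings is stated before diagnoses are released

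*Protocol article*

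**What the plan says.** The Study Design section calls the study assessor-blinded and defines the test under evaluation broadly: "the EEG and the algorithms used to analyze the EEG data will be regarded as the index test". The same section gives the only masking commitment for the people who process the signal: "the team in charge of EEG processing will not have access to the clinical diagnosis data during data collection for the study".

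Other sections separate roles as follows:

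- Diagnostic Performance of the Index Test: "Clinical information and reference standard results will not be available to the performers of the index test". It adds that "performers of the index test will neither be involved in the technological processing nor the statistical analyses".
- Planned Data Analysis: "the physicians involved in diagnosing and selecting the study groups will not participate in the analysis".
- Study Design: the principal investigator, who sets the reference diagnosis, neither analyses EEG data nor sees EEG results.

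Three further statements bear on the processing work. A tertiary objective is "To optimize the preprocessing automatic system for artifact removal in EEG signals". Missing data are not imputed, analyses use complete cases, and the sample size carries a margin ("10% added for nonassessable data-complete-case analysis"). The classification algorithm is developed against the three diagnostic groups (Analysis of Primary Parameters), so labels must be released to the technical side at some point.

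**The concern.** In an accuracy study with a machine-learning index test, what happens between raw recording and classifier input is part of the test. Two kinds of decision in that interval can involve judgement: how the signal is cleaned, and whether a recording is usable. If they are made with the diagnosis known, they can drift, without intent, towards keeping recordings that look typical of their group and removing those that do not. The primary sensitivity and specificity would then be too favourable.

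Labels are needed to train the classifier. They are not needed to clean a signal or judge its quality. The natural end of masking for processors is therefore completion of those steps, not the end of data collection. The article picks the earlier point. Recruitment ended on December 11, 2024 (Results), so the promised window has probably closed or is about to.

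**Working it through.** **1. Does any other statement mask the processors after data collection?**

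| Section | Who is restricted | Reaches the processors after collection? |
|---|---|---|
| Study Design | EEG-processing team, during data collection | No, the window ends there |
| Study Design | Principal investigator, kept from EEG results | No, protects the reference standard |
| Planned Data Analysis | Diagnosing physicians, kept out of analysis | No |
| Diagnostic Performance of the Index Test | Performers of the index test, no time limit | No, performers are kept out of technological processing |

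No section says that preprocessing or the assessable set is complete before diagnoses become available.

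**2. How much data can leave as nonassessable?** Study Visits (Third Visit) gives 40 per group, plus 10 per group, plus 10%, for a total of 162. This reproduces with the 10% taken on the 40: 3 × (40 + 10 + 4) = 162, or 54 per group, that is 108 ADHD cases and 54 controls. The margin is thus 4 per group (8 cases, 4 controls). If 10% of all recruited children were lost, it would be about 11 cases and 5 controls. The base of 120 cannot be re-derived because its inputs are in an appendix that is not shown.

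**3. What would exclusions do to the estimates?** Let n be the group size, p the true proportion correctly classified, e the number excluded and s the share of exclusions that fall on misclassified children. The expected estimate is

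(n·p − e·(1 − s)) / (n − e).

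If exclusion is unrelated to classification, s = 1 − p and the estimate equals p. A difference in exclusion rates between diagnostic groups does not by itself bias sensitivity or specificity. Within a group, exclusion must be related to how the child would be classified.

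For sensitivity take p = 0.80, the null boundary in Hypotheses (0.90 − 0.10). For specificity p = 0.80 is an assumption, because the article gives no value for the false-positive threshold.

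| Group | n | e | s = 0.20 (neutral) | s = 0.60 | s = 1 |
|---|---|---|---|---|---|
| Cases | 108 | 8 | 0.800 | 83.2/100 = 0.832 | 86.4/100 = 0.864 |
| Cases | 108 | 11 | 77.6/97 = 0.800 | 82.0/97 = 0.845 | 86.4/97 = 0.891 |
| Controls | 54 | 4 | 0.800 | 41.6/50 = 0.832 | 43.2/50 = 0.864 |
| Controls | 54 | 5 | 0.800 | 41.2/49 = 0.841 | 43.2/49 = 0.882 |

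**4. Reading the table.** The s = 1 column requires every excluded child to be one the classifier gets wrong. Knowing the diagnosis is not enough for that; the classifier output must be known too. The column is an upper bound for exclusion after classification, not the effect of the masking window. The documents contain nothing from which to choose s between neutral and this bound.

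**The case against.** The strongest reply is that the sentence promises something and forbids nothing. It does not say that processors will see diagnoses before cleaning is finished. Masking must end at some point so that the algorithm can be trained, and a lock before label release may well be in the full protocol (version 4.0) or an analysis plan, neither of which is shown. This stands as a limit on what can be claimed. It does not remove the point, because the article states when masking ends and places that end at the close of data collection.

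Other replies also have weight:

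- Artifact removal is described as automatic, which limits case-by-case discretion. Its optimisation is a tertiary, exploratory aim (Statistical Analysis), and nothing says that the optimised version feeds the primary analysis. Nor is it stated who judges assessability. But tuning an automatic system is still a choice, and automation does not settle which recordings count.
- Indeterminate index results are not allowed (Planned Data Analysis). This governs the positive or negative call. The same section still keeps a margin for nonassessable data.
- A reader might infer that out-of-sample validation cannot help. That is too strong. It would protect against tuning done inside training data and applied unchanged to held-out children. It would not recover recordings removed beforehand with labels known. The article does not describe the validation scheme, so neither case can be assumed.
- The masking of the investigator, the diagnosing physicians and the index-test performers is unaffected, so the assessor-blinded label is incomplete for one team, not false.

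**Conclusion.** The point holds as a defect in the stated masking window: the text permits cleaning choices and assessability calls to be made with diagnoses known, in a step that belongs to the index test. It is a moderate, avoidable risk of bias in the primary sensitivity and specificity, worth correcting because correction is cheap.

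Its size is not determined by the documents. It runs from no bias, when exclusions are unrelated to classification, towards an upper bound that the masking window alone would not produce. A reader might go further and infer that the results will be inflated, for example specificity from 44/54 = 81.5% to 44/50 = 88.0% with 4 of 10 false positives dropped, or sensitivity from 92/108 = 85.2% to 92/100 = 92.0% with 8 of 16 misses dropped. The documents do not support that. The error counts are assumed, every exclusion is placed on a misclassified child, and nothing suggests that exclusions will be made after classifier output is seen.

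**What to change.** Amend the sentence in Study Design so that the processing team stays masked to diagnosis and to recruitment source until three steps are complete: artifact-removal settings are frozen, every recording has been cleaned with them, and the list of assessable recordings is dated and signed. All three should precede any classifier output. Labels are then released for training. Recruitment source belongs in the sentence because cases and controls come from different sources (Participant Recruitment), so the source largely reveals the group.

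Keep any later preprocessing optimisation out of the primary analysis, or tune it inside training folds only. Report the number of nonassessable recordings by diagnostic group.

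If labels have already been released, masking cannot be restored by rewording. State when release happened relative to the three steps, and add a sensitivity analysis that uses label-independent automatic cleaning and exclusion rules.

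The change needs no further participants or visits, and the planned 162 stands. The cost is that label release waits for the lock and, if labels are already out, the work of the added analysis.

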#### Third Visit

During the third visit, the suspension of medication and abstinence from stimulant substances such as caffeine and xanthines will be again verified. Once both are confirmed, the neuropsychological evaluation will proceed with the administration of the CPT-3, the ENFEN, and additional tests to screen for comorbid conditions, such as PROLEXIA.

Although the sample size calculation indicates a total of 120 participants (40 per group), an additional 10 participants per group will be recruited to explore factors influencing diagnostic performance and SCT construct validity (Figure 1). Furthermore, an extra 10% will be added to account for nonassessable data, resulting in a total of 162 participants. This total may be slightly increased to ensure 54 participants per group after accounting for screening failures and protocol deviations. The maximum time interval between the index test and the reference standard is 72 hours; however, whenever feasible, a 24-hour interval will be pursued.

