#### Statistical Analysis

The primary objective will be to assess the diagnostic accuracy of the index test in terms of classification probabilities, specifically sensitivity and specificity. Sample size calculation ensures a minimum performance threshold within the target population.

This objective is interdependent with another primary aim, identifying the minimal set of biomarkers that optimize the diagnostic performance of the index test. As this objective does not involve hypothesis testing, adjustments for multiplicity are unnecessary.

The analyses of the secondary objectives will be exploratory, except for the first, which shares the hypothesis-free nature of biomarker identification. Tertiary objectives will also be exploratory, focusing on the validity of the SCT construct and EEG signal preprocessing systems. These analyses may be expanded in future studies to identify EEG-based clusters associated with ADHD symptomatology.

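### CPT-3 helps form the reference diagnosis and is then judged against it, so the exploratory index-test versus CPT-3 comparison is biased in favour of CPT-3 by an unknown amount

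*Protocol article*

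**What the plan says.** **CPT-3 is inside the reference.** Under Study Design the reference is defined thus: "The best estimated diagnosis based on clinical interviews and neuropsychological assessment will be regarded as the reference test". The same section assigns groups "based on clinical evaluation including the reference CPT-3". The Abstract (Methods) agrees: the best estimated diagnosis is "based on clinical interviews and a neuropsychological assessment that includes the Conners Continuous Performance Test". The Third Visit section places the test in that work-up: "the neuropsychological evaluation will proceed with the administration of the CPT-3, the ENFEN".

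**CPT-3 is also the comparator.** The third secondary objective (Introduction) compares the performance of the index test "with that of the Continuous Performance Test Third Edition (CPT-3". The only standard it names is the PI's final diagnosis. The Abstract (Conclusions) gives the expected result: "The EEG-based ADHD diagnosis is expected to have greater sensitivity and specificity than the Conners Continuous Performance Test".

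**Status.** The Statistical Analysis section states: "The analyses of the secondary objectives will be exploratory, except for the first". The CPT-3 comparison is the third, so it is exploratory.

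**Safeguards.** Study Design and Strengths and Limitations keep the PI blind to EEG and algorithm output. No blinding to CPT-3 is stated. The circularity admitted under Strengths and Limitations is that one diagnosis serves as both training label and reference. It does not mention CPT-3.

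**The concern.** When one of two competing tests contributes to the truth that scores both, that test cannot be wrong in any child where it decided the diagnosis. The other test is charged with an error in every such child where the two disagree. CPT-3 therefore looks better than it is. The index test can look worse, unless it tends to make the same errors as CPT-3.

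At stake is what the third secondary objective can conclude. The Abstract expects EEG to be better on both sensitivity and specificity. With CPT-3 in the reference, a real EEG advantage on one of these could disappear or change sign, and the trial would have no planned analysis to show why.

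**Working it through.** The article gives no accuracy for CPT-3 and no weight for it in the diagnosis, so there is no planned figure to reproduce. The calculation below is an illustration.

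**Inputs**
- Share with ADHD: 2/3, from three equal groups, two of them ADHD (Third Visit section).
- Assumed accuracy against a diagnosis made without CPT-3: CPT-3 0.60/0.75 and EEG 0.90/0.80 (sensitivity/specificity).
- Assumed: errors of the two tests are independent given true status.
- Assumed: with probability w the diagnosis R equals the CPT-3 result C; otherwise it equals the CPT-free status T. E is the EEG result.

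**Building blocks**
- P(C=1) = 2/3 × 0.60 + 1/3 × 0.25 = 0.4833; P(C=0) = 0.5167
- P(C=1,E=1) = 2/3 × 0.60 × 0.90 + 1/3 × 0.25 × 0.20 = 0.3767
- P(C=0,E=0) = 2/3 × 0.40 × 0.10 + 1/3 × 0.75 × 0.80 = 0.2267

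**w = 0.10**
- P(R=1) = 0.9 × 0.6667 + 0.1 × 0.4833 = 0.6483; P(R=0) = 0.3517
- CPT-3 sensitivity = (0.9 × 0.4000 + 0.1 × 0.4833)/0.6483 = 0.630
- CPT-3 specificity = (0.9 × 0.2500 + 0.1 × 0.5167)/0.3517 = 0.787
- EEG sensitivity = (0.9 × 0.6000 + 0.1 × 0.3767)/0.6483 = 0.891
- EEG specificity = (0.9 × 0.2667 + 0.1 × 0.2267)/0.3517 = 0.747

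**Results by w**

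| w | CPT-3 | EEG | EEG minus CPT-3 |
|---|---|---|---|
| 0 | 0.600/0.750 | 0.900/0.800 | +0.300/+0.050 |
| 0.05 | 0.615/0.769 | 0.896/0.773 | +0.281/+0.004 |
| 0.10 | 0.630/0.787 | 0.891/0.747 | +0.261/-0.040 |
| 0.20 | 0.661/0.820 | 0.881/0.699 | +0.220/-0.121 |

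Few children need to be affected. At w = 0.10 the diagnosis changes only where CPT-3 is wrong, which has probability 2/3 × 0.40 + 1/3 × 0.25 = 0.35. Of 165 enrolled that is 165 × 0.10 × 0.35 = 5.8 children.

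**Direction.** In this model the apparent specificity difference is

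[(1-w) P(T=0) (true difference) - w P(C=0,E=1)] / P(R=0), where P(R=0) = (1-w) P(T=0) + w P(C=0).

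The subtracted term is never negative, and the denominator is at least (1-w) P(T=0). Any apparent EEG advantage is therefore no larger than the true one, whatever the error correlation. Sensitivity has the same form. At w = 0.10, P(C=0,E=1) = 0.5167 - 0.2267 = 0.29, which gives (0.015 - 0.029)/0.3517 = -0.040, as in the table.

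**Sensitivity to the assumptions**
- CPT-3 0.70/0.70 and EEG 0.90/0.80, independent errors: the true +0.200/+0.100 becomes +0.126/-0.053 at w = 0.20.
- Same accuracies, error correlation at its maximum: +0.155/0.000 at w = 0.20.
- Both tests truly 0.70/0.70, w = 0.30: the apparent difference is -0.099/-0.173 with independent errors, -0.049/-0.087 at half the maximum correlation, and 0/0 at the maximum.

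**The case against.** **The weight of CPT-3 may be small.** The diagnosis also rests on interviews and on other instruments (WISC-V, ENFEN, PROLEXIA), and Strengths and Limitations says that for several patients the PI only confirmed an earlier diagnosis. This stands. It limits what can be said about size, not about existence or direction.

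**The two tests may share errors.** Both are go/no-go tasks, and correlated errors shrink the bias. This also stands, but in the runs above the bias vanished only when the tests were equally accurate and their errors maximally correlated.

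**Sensitivity survives, and the comparison is exploratory.** In the illustration EEG stays well ahead on sensitivity, and the specificity reversal is helped by an assumed true gap of only 0.05. The Abstract states an expectation, not a confirmatory claim. Both points stand and keep the severity moderate.

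**Tempting stronger readings.** A reader might infer that the comparison cannot support the Abstract's conclusion, or is uninterpretable whichever way it falls. The documents do not support that: this bias works against EEG, so it would not produce an EEG advantage. A reader might add an opposing bias, since CPT-3 has a fixed program cut-off while the algorithm is developed on these children. The article does say that the algorithm is developed on these groups, but not that its accuracy will be estimated in-sample. Validation details may sit in documents not shown, so that argument is not relied on here.

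**Conclusion.** The point holds in a limited form. As written, the exploratory comparison has incorporation bias that favours CPT-3. That rests on the article's own definitions of reference and comparator. The size is unknown and depends on how much CPT-3 moves the diagnosis, on the true accuracies, and on how far the tests' errors overlap.

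Under the stated assumptions, following CPT-3 in 10% of children turns a true +0.05 specificity advantage into about -0.04, while the sensitivity difference only falls from +0.30 to +0.26. An observed EEG advantage would be conservative on this point. What could not be trusted is the size of the difference, CPT-3's absolute accuracy, and any null or reversed result. The change should be made; it does not affect the confirmatory test.

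**What to change.** 1. Keep the comparison against the PI diagnosis, labelled as biased in favour of CPT-3, with the reason given.
2. Add a paired sensitivity analysis, with both tests in the same children, against a reference that does not contain the study CPT-3: recruitment status fixed before the third visit (pre-study ADHD diagnosis versus paediatric control). Children should keep their recruitment status even if the study work-up changed it; otherwise CPT-3 re-enters through selection.
3. Before that, check in the records whether the earlier diagnoses used a CPT.
4. Word the expectation in the Abstract (Conclusions) as exploratory and subject to this bias.

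**Cost.** One added analysis on existing data, a records check and some wording. Prospectively selected cases without a prior diagnosis drop out of the sensitivity analysis. Recruitment status may also misclassify some children: Table 1 allows diagnoses up to three years old, which Participant Recruitment says the study work-up is to confirm, and unrecognised ADHD among controls may come to light only in that work-up. It is therefore suited to a labelled sensitivity analysis, not to being the sole basis for a claim.
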